### **6.3. EXCLUSION CRITERIA**

1. Evidence of androgen deficiency at baseline (those below the normal male reference range of T<10nmol/L at our hospital laboratory);
2. Contraindications to spironolactone, cyproterone acetate or E2 therapy including active renal, cardiac, or liver disease, severe depression, hyperkalaemia, thromboembolic disease or estrogen-sensitive malignancy, meningioma, or planned removal of testes during the study;

### **6.4. CONSENT**

Individual informed consent will be obtained from each participant prior to any part of the study being undertaken. Participants will be provided with a copy of the signed Participant Information Consent Form.

## **7. PARTICIPANT SAFETY AND WITHDRAWAL**

## 7.1. RISK MANAGEMENT AND SAFETY

While we do not anticipate a compromise in safety, there is the risk that tests performed may be distressing (physically or psychologically) or there may be risks that researchers could not reasonably anticipate. Trained staff will perform all tests to minimise risk.

### 1. Possible risks associated with taking anti-androgen agents

Depression is a potential side-effect of cyproterone, although it is unclear whether this is related to the drug itself or the T lowering effect (15). Clinically, benefits of treatment on depression far outweigh any risk. Rare reports of hepatitis have been reported with high-dose ( $150 \pm 50$  mg/day) cyproterone acetate. As a safety precaution, we will monitor for depression and liver function and only use low-dose (12.5mg/day). Spironolactone is a diuretic and can cause hyperkalaemia in individuals with renal impairment, although no measurable effect of clinical significance in otherwise healthy individuals. We will monitor blood pressure, renal function (urea, creatinine), and potassium levels to ensure safety. Hyperkalaemia is rare in the setting of normal renal function (no cases observed in our retrospective study [n=38 on spironolactone]) and should not affect blinding. Adverse events will be actioned as per Ethics Committee guidelines. Participants will be withdrawn if they meet the criteria for exclusion, or have a change in safety assessments that necessitate clinical intervention.

### 2. Psychological distress

While we do not envisage this study will cause any participant psychological distress, questionnaires to monitor for depression (PHQ-9 (20) ) and gender dysphoria (GPSQ(21)) will be used. These safety assessments will be performed at baseline, 3 and 6 months. Participants will be encouraged to speak to the study doctors if they experience distress. An appropriate level of care will be triaged by the study doctors. This might include withdrawal from the study, referral for treatment at Austin Health or similar health network.

### 3. Risks associated with bloods tests

Venepuncture can cause some discomfort and bruising.

## 7.2. HANDLING OF WITHDRAWALS

Participants who have chosen to or are asked to withdraw from the study will be reviewed by a study doctor to ensure they are given information about ongoing clinical care. They will be asked to sign the Withdrawal of Participation form (PICF). It will be made clear to them through the trial and at that time that withdrawal will have no negative impact on their relationship with their treating doctors, or Austin Health. No additional personal or health or samples information will be collected from participants once they have withdrawn.

Consistent with an intention-to-treat analysis, any data that has been collected up to the point of withdrawal (of loss to follow up for other reasons) will be included in data analysis. Similarly, all biological specimens will need to be analyzed so that the intention-to-treat principle is not violated.

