### **5.4.2 Safety assessments and withdrawal (performed at baseline, 1,2,3, and 6 months)**

Questionnaires to monitor for depression (PHQ-9) and gender dysphoria (GPSQ)(21) will be used. Blood pressure, medical conditions and medication use will be recorded each visit. Serum urea, electrolytes and creatinine will be monitored to assess for risk of hyperkalaemia, dehydration or renal impairment which may occur with spironolactone. An ECG will be performed at baseline and 6 months to monitor the QTc, prolongation of which has been associated with androgen deprivation therapy in men with prostate cancer. (28) Adverse events will be actioned as per Ethics Committee guidelines. Participants will be withdrawn if they meet the criteria for exclusion, or have a change in safety assessments that necessitate

clinical intervention. A further blood test at months 1 and 2 will be obtained to monitor the E2 valerate dose to ensure serum E2 remain in the target range.

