### 8.3. STATISTICAL METHODS TO BE UNDERTAKEN

We will use a Generalised linear mixed model with a restricted maximum likelihood function to determine between group differences in the main outcome measures over time, adjusted for randomisation strata. Further analysis will include outcomes as a quantitative measure, using Generalised additive mixed models to examine non-linear (spline) effects of hormone treatments over time, adjusted for randomisation strata. The estimated marginal means across each timepoint plus 95% CI between the groups from baseline to study end will be determined, and p values  $< 0.05$  are considered statistically significant. Following an intention-to-treat protocol, the analysis will include all randomised subjects who are enrolled in the trial.

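### Participants withdrawn for safety reasons are barred from all later measurement, so their month-6 breast volume is lost and the promised intention-to-treat comparison leans on a missing-at-random assumption

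*Protocol*

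**What the plan says.** **Who is withdrawn.** Protocol 7.1, repeated in 5.4.2: "Participants will be withdrawn if they meet the criteria for exclusion, or have a change in safety assessments that necessitate clinical intervention". The exclusion criteria in 6.3 that thereby become withdrawal triggers include "active renal, cardiac, or liver disease, severe depression, hyperkalaemia".

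**What follows withdrawal.** Section 7.2 applies both to people who choose to leave and to people who are asked to leave. For all of them: "No additional personal or health or samples information will be collected from participants once they have withdrawn". The same section says that, in keeping with intention-to-treat, the analysis will use "any data that has been collected up to the point of withdrawal".

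**What the analysis promises.** Section 8.3: "Following an intention-to-treat protocol, the analysis will include all randomised subjects who are enrolled in the trial".

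**When the outcomes are measured.** The visit table in 5.1 and the procedures table in 5.2 place chest photography (the source of breast volume) and DXA at months 0 and 6 only. The heading of 5.4.1 gives baseline, 3 and 6 months for the measurements listed under it, which include breast size and DXA. These places disagree.

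**Which effects are tied to which drug.** Section 7.1: "Depression is a potential side-effect of cyproterone". Section 5.4.2 has blood chemistry monitored "to assess for risk of hyperkalaemia, dehydration or renal impairment which may occur with spironolactone".

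**The concern.** The protocol describes no status in which a participant has stopped study drug but is still followed. A person removed under the safety rule, who may be quite willing to return at month 6, falls under the same ban on further data as someone who has withdrawn consent.

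This matters most for the primary endpoint. With photography at months 0 and 6 only, withdrawal at month 1, 2 or 3 leaves a baseline value and nothing else. The same holds for DXA fat mass. The month-6 testosterone, PHQ-9 and GPSQ values are lost too, although those outcomes keep any month-3 value already taken.

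If the people lost differ from those retained, and differ more in one arm than the other, the month-6 comparison is biased. Section 7.3 treats attrition purely as a matter of power. Enrolling more people protects precision but does not remove such bias.

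**Working it through.** **1. The plan's own figures.** Section 8.1 uses 48% versus 90%, power 0.9 and significance level 0.05, and states 25 per group. The two-sided pooled-variance formula for two proportions, with mean proportion 0.69, gives

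n = [1.960 × √(2 × 0.69 × 0.31) + 1.282 × √(0.48 × 0.52 + 0.90 × 0.10)]² / 0.42² = 23.3, rounded up to 24 per group.

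This agrees with the stated 25 to within one. Inflating for 20% dropout: 25 / 0.80 = 31.25, rounded up to 32 per group, or 64 in total. The dropout arithmetic is right, so the point is not about the number enrolled.

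**2. How many outcomes could be missing.** At the planned attrition, 64 × 0.20 = 12.8 participants, about 13, would lack a month-6 value. About 51 would remain, or 25.6 per arm. The 20% is all-cause dropout, which section 8.1 sets against 15% in an observational study. It is not a rate of safety withdrawal, and the protocol gives no such rate. Some of the 13 would refuse follow-up or be lost under any rule, so 13 is an upper limit on what changing the rule could recover.

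**3. What a withdrawn person gives the model.** On the visit tables there is one post-baseline breast measurement. A baseline-only participant can be listed in the mixed model but carries essentially no information on the month-6 difference. That difference is estimated from those retained, and it applies to everyone randomised only if the missing values are missing at random given what was observed.

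**4. Bias formula.** For each arm let f be the share lost and k the month-6 mean of those retained minus that of those withdrawn, in SD units, after allowing for baseline and strata. The mean of those retained differs from the mean of the whole arm by f × k. The bias in the arm comparison is therefore

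f₁k₁ − f₀k₀.

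**5. Range.** Section 8.1 says there are no preliminary data on breast size, and no withdrawal rates by arm are given. Both f and k below are therefore assumptions, with the gap placed in one arm only.

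| Share lost in that arm | People (of 32) | Gap 0.5 SD | Gap 1.0 SD |
|---|---|---|---|
| 5% | 1.6 | 0.025 SD | 0.05 SD |
| 20% | 6.4 | 0.10 SD | 0.20 SD |

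If loss is equal and equally informative in both arms, f₁k₁ = f₀k₀ and the bias is zero.

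**6. Effect on the test.** With 25.6 observed per arm the standard error is √(2/25.6) = 0.28 SD. By the normal approximation, a bias of 0.10 SD raises a two-sided 5% type I error to about 6.5%, and 0.20 SD raises it to about 11.0%.

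**The case against.** Much of the case on the other side stands, and it rules out several stronger readings.

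*That loss is informative and differs by arm.* A reader might infer this from the adverse effects attached to each drug. The withdrawal rule is worded identically for both arms. Section 7.1 calls hyperkalaemia rare with normal renal function and reports no cases among 38 people on spironolactone. It calls depression only a potential effect of cyproterone and leaves open whether the drug or the lowered testosterone is responsible. Nothing in the protocol links either event to breast volume. Informative loss is a supported risk, not a demonstrated fact.

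*That the rule costs 13 participants.* It does not; 13 is all-cause attrition. The subset withdrawn for safety is unstated and may be small.

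*That PHQ-9 will look better in the arm with more depression withdrawals.* No PHQ-9 cut-off triggers withdrawal, and section 7.1 lists withdrawal as one possible response to distress. A high month-3 score that led to withdrawal is already recorded and kept, and a mixed model uses it. Scores after withdrawal could go either way, so the direction is not established.

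*That intention-to-treat cannot be delivered at all.* The mixed model can nominally include everyone with data. If 5.4.1 rather than the tables is right about timing, people withdrawn after month 3 also contribute a post-baseline breast value. What is missing is the observed month-6 value.

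*That every participant who stops capsules must leave.* The protocol does not say so. The conflict is with those withdrawn from the study under 5.4.2, 7.1 and 7.2.

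One defence fails: that this can be left to the statistical analysis plan. Such a plan can add sensitivity analyses, but it cannot recover measurements that the protocol forbids taking.

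**Conclusion.** The point holds as a design weakness of unknown size. A rule in the current text discards month-6 outcomes from people who may be willing to provide them, while 7.2 and 8.3 promise an intention-to-treat analysis of everyone randomised. On the visit tables, that analysis depends on a missing-at-random assumption for every early withdrawal.

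Under the assumptions shown, the bias is about 0.025 to 0.20 SD if the informative loss is confined to one arm, and zero if it is balanced. The upper end uses the whole planned attrition and a full 1 SD gap, so it should not be read as an expected value. Neither the amount nor the direction can be taken from the protocol. The case for changing the rule is that the loss is avoidable, cannot be repaired afterwards and costs little to prevent.

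**What to change.** - In 5.4.2, 7.1 and 7.2, leave the clinical stopping criteria as they stand, but distinguish stopping study drug from withdrawing consent to follow-up.
- Invite those who stop study drug, and who agree, to the remaining scheduled assessments: at least month 6 (chest photography, DXA, PHQ-9, GPSQ, bloods), and month 3 where it is still ahead. Analyse them in their randomised arm.
- Apply the ban on further data in 7.2 only to participants who withdraw consent.
- Record whether each departure is a drug stop, a consent withdrawal or loss to follow-up, with date and reason, so that loss can be reported by arm.
- Reconcile the timing of breast and DXA measurement between the tables in 5.1 and 5.2 and the heading of 5.4.1.

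The cost is protocol and consent-form wording, plus visits already in the schedule for at most about a dozen people. The downside is that outcomes measured after stopping dilute a pure on-drug contrast; that is inherent in the intention-to-treat comparison the protocol says it wants.

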### 7.3. REPLACEMENTS

The study is adequately powered to determine the primary endpoints accounting for 20% attrition and withdrawn participants will not be replaced.

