### 4.3. OUTCOME MEASURES

#### 1. Primary Endpoint

- Breast volume

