#### 2. Secondary endpoints

- Percentage of individuals who have total T levels < 2 nmol/L (above the female reference range) at 3 and 6 months. ;
- Fat mass including leg and gynoid regional fat;
- Patient Health Questionnaire 9 (PHQ-9) (20)
- Gender dysphoria using the Gender Preoccupation and Stability Questionnaire (GPSQ) (21).

**Covariates:** Age and Body Mass Index (BMI, kg/m^2)

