## 8. STATISTICAL METHODS

### 8.1. SAMPLE SIZE ESTIMATION & JUSTIFICATION

Based on the percentage of individuals that suppress  $T < 2\text{nmol/L}$ , for a difference of 40% (estimated from our data, 48% in spironolactone group vs 90% in cyproterone), a sample size of 25 per group is required (power 0.9 and level of significance 0.05). Based on a conservative drop-out rate of 20% (our current observational bone health study in transgender individuals has a dropout rate of 15%), it is estimated that a total of 64 participants will be required for enrolment into the study to be powered, to show a difference in total testosterone concentrations between groups. We do not have any preliminary data on breast size.

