### 8.2. POWER CALCULATIONS

Power calculations are based on the means and standard deviation determined for the secondary endpoint from our preliminary data.

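### Section 7.3 claims adequate power for the primary endpoint, but the only calculation is for a secondary endpoint, so power for breast volume is unknown

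*Protocol*

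**What the plan says.** - **Primary endpoint.** The synopsis and section 4.3 list one primary endpoint: "Breast volume".
- **Secondary endpoint.** The first secondary endpoint in section 4.3 is "Percentage of individuals who have total T levels < 2 nmol/L", at 3 and 6 months.
- **Power claim.** Section 7.3 says "The study is adequately powered to determine the primary endpoints accounting for 20% attrition", and in the same sentence rules out replacing withdrawn participants.
- **Sample size.** Section 8.1 works from the testosterone proportions, "for a difference of 40% (estimated from our data, 48% in spironolactone group vs 90% in cyproterone", and concludes that "a sample size of 25 per group is required (power 0.9 and level of significance 0.05". It allows for 20% dropout, arrives at 64, and says these are needed to show a difference in testosterone. It closes with "We do not have any preliminary data on breast size".
- **Basis of power.** Section 8.2 says: "Power calculations are based on the means and standard deviation determined for the secondary endpoint from our preliminary data".

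**The concern.** Section 7.3 credits the design with a property for its primary endpoint that sections 8.1 and 8.2 show was never assessed. No target difference, SD or power for breast volume appears anywhere in the protocol, and 8.1 says there were no data from which to derive them.

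The main risk is in how the primary result is read. If breast volume does not differ significantly between arms, 7.3 can be cited to call this a negative finding from an adequately powered trial. The protocol gives no basis for that description.

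There is a smaller slip beside it. Section 8.2 describes a calculation from means and an SD, whereas 8.1 compares two proportions.

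**Working it through.** **1. Reproduce the plan's own figure (secondary endpoint)**

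Inputs from 8.1: p1 = 0.48, p2 = 0.90, power 0.90, alpha 0.05. Sidedness is not stated, so two-sided is taken. The text calls the difference 40%, although 90 − 48 = 42 points.

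Two proportions, pooled variance under the null, no continuity correction:

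n = [z(0.975)·√(2·p̄(1−p̄)) + z(0.90)·√(p1(1−p1) + p2(1−p2))]² / (p2−p1)², with p̄ = 0.69

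- First term: 1.960 × √0.4278 = 1.282
- Second term: 1.2816 × √0.3396 = 0.747
- n = (2.029)² / 0.1764 = 23.3, so 24 per group against the stated 25

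Other common formulas give about 21 (unpooled), 23 (arcsine) and 28 (continuity-corrected), so 25 is reasonable.

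Dropout: 25 / 0.8 = 31.25, so 32 per arm and 64 in total, as stated.

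**2. Look for the same inputs for breast volume**

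| Input | Testosterone < 2 nmol/L (secondary) | Breast volume (primary) |
|---|---|---|
| Assumed values per arm | 48% and 90% | none |
| SD or target difference | not needed | none |
| Power | 0.9 | none |
| Preliminary data | yes | stated not to exist |

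Power for breast volume cannot be computed from the document. The claim in 7.3 has nothing behind it for the endpoint it names.

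**3. Illustration in SD units**

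Assumptions: two-sample t-test, two-sided 5%, SD = 1. Completers: 64 × 0.8 = 51.2, about 25 to 26 per arm.

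By the normal approximation, the detectable difference is (z(0.975) + z(power))·√(2/n). At n = 25:

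- 80% power: 2.802 × 0.283 = 0.79 SD (0.81 by the t distribution)
- 90% power: 3.242 × 0.283 = 0.92 SD (0.94 by the t distribution)

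With all 64 observed (32 per arm), the t-test figures are 0.71 and 0.82 SD.

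Adjusting for baseline breast volume multiplies the detectable difference by √(1−r²), where r is the assumed baseline to follow-up correlation. At 25 per arm and 80% power:

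| Assumed r | √(1−r²) | Detectable difference (SD) |
|---|---|---|
| none | 1 | 0.81 |
| 0.3 | 0.954 | 0.77 |
| 0.5 | 0.866 | 0.70 |
| 0.7 | 0.714 | 0.58 |

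Power for a true difference of 0.5 SD at 25 per arm is 41% unadjusted. At r = 0.7 the effective difference is 0.5 / 0.714 = 0.70 SD, giving 68%.

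The unadjusted 95% CI half-width at 25.6 per arm is t(0.975)·√(2/n) = 2.01 × 0.280 = 0.56 SD.

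**The case against.** **The statistics section is candid.** Sections 8.1 and 8.2 say openly that the size rests on testosterone and that breast data are lacking. The error is one clause in a section on replacements, and anyone who reads section 8 will not be misled. This bears on how much damage the clause does, but it remains wrong as written. Nor can an unseen SAP repair it, because 7.3 makes a positive claim and 8.1 says the data to support such a claim did not exist.

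**A reader might infer that the trial can detect only a large breast volume difference, or is underpowered for it.** The document does not support that. The 0.81 SD figure assumes an unadjusted t-test on about 51 completers, not on all 64. Section 8.3 plans a mixed model over time, and breast imaging is scheduled at baseline and 6 months, so baseline information may sharpen the comparison. With no SD, correlation or target difference, nobody can say whether 0.6 or 0.8 SD is large in relation to the true effect. This objection stands in full: the defensible statement is that power is unknown.

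**A reader might infer that 64 is miscalculated.** It is not; it reproduces for the endpoint that set it.

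**A reader might infer that the no-replacement rule falls with the power claim.** It need not. Enrolment was inflated for 20% dropout on the testosterone endpoint, and the rule can rest on that.

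**Estimation is already planned.** Section 8.3 provides estimated marginal means with 95% CIs, and nowhere does the protocol propose to read non-significance as equivalence. That also stands, so no new analysis is needed.

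**Conclusion.** The concern holds as an internal contradiction: 7.3 asserts adequate power for the primary endpoint, while 8.1 and 8.2 show that the only calculation concerns a secondary endpoint and that no breast data were available. This conclusion rests on the text alone and needs no assumption about effect size.

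Its practical size can only be illustrated. With about 25 completers per arm, 80% power corresponds to roughly 0.8 SD unadjusted, or roughly 0.6 to 0.8 SD with baseline adjustment at assumed correlations of 0.7 to 0.3. Those figures assume a two-group comparison at two-sided 5% and correlations that the protocol does not give. They show why the claim of adequate power cannot be taken for granted; they do not show that it is false for the true effect.

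The mismatch in 8.2 between means with an SD and the proportions used in 8.1 is a separate, minor wording error that can be corrected at the same time.

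**What to change.** **Section 7.3.** Replace the power claim with:

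> The sample size allows for 20% attrition for the secondary endpoint, the proportion with T < 2 nmol/L; power for the primary endpoint, breast volume, is not established.

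The no-replacement rule can stay, resting on the 20% inflation in 8.1.

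**Section 8.2.** Refer to proportions instead of means and an SD, and add, as illustration only:

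> With about 25 completers per arm and two-sided 5% significance, 80% power corresponds to a breast volume difference of about 0.8 SD unadjusted, or about 0.6 to 0.8 SD with baseline adjustment at assumed correlations of 0.7 to 0.3; no SD is available, so a non-significant primary result should be interpreted from its 95% CI.

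**Cost.** Wording in two sections, and a less favourable stated position on the primary endpoint. Sample size, endpoints, analysis model and participant numbers do not change.

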## 8. STATISTICAL METHODS

### 8.1. SAMPLE SIZE ESTIMATION & JUSTIFICATION

Based on the percentage of individuals that suppress  $T < 2\text{nmol/L}$ , for a difference of 40% (estimated from our data, 48% in spironolactone group vs 90% in cyproterone), a sample size of 25 per group is required (power 0.9 and level of significance 0.05). Based on a conservative drop-out rate of 20% (our current observational bone health study in transgender individuals has a dropout rate of 15%), it is estimated that a total of 64 participants will be required for enrolment into the study to be powered, to show a difference in total testosterone concentrations between groups. We do not have any preliminary data on breast size.

